#### Acupoints

The choice of acupoints was based on a literature review and clinical practice. A survey conducted in 2010 by the School of Chinese Medicine at HKBU revealed that 60 % of patients who were suffering from AR or asthma found their symptoms were alleviated after receiving TJ therapy. Amongst the 812 people receiving TJ therapy, 558 (approximately 70 %) were suffering from AR or asthma. The survey covered 224 AR patients and 57 asthma patients, and found that 60 % of each group reported that their symptoms were relieved [20]. The latest clinical study conducted in 2014 revealed that more than 50 % of patients suffering from AR obtained benefit after receiving TJ therapy. The study found that, among the 3438 patients included in the survey, 52–67 % of the patients with AR found that their symptoms were alleviated and 32–50 % of those surveyed reported that their body constitution had been improved [21].

Five acupoints will be used: *Dazhui* (GV 14), *Feishu* (UB 13) and *Shenshu* (UB 23), on both sides of the body. A TJ patch will be applied to each acupoint, and left on for 2 hours. A 4 cm^2^ piece of hypoallergenic tape will be used to stick one patch on one acupoint. After 2 hours the patches will be removed by our Chinese medicine practitioner (CMP). If a participant cannot tolerate the stimulation or suffers a allergic reaction, the patching time can be appropriately shortened. Names and details of acupoints are listed in Table 2.

**Table 2 Tab2:** Acupoints used in the study

Name of acupoints	Areas	Special qualification	Effects of stimulation	Indications
*Dazhui* (GV 14)	In a depression below the processus spinosus of the 7th cervical and above the 1st thoracic vertebrae	A crossing point by which the leading sinartery communicates with all *yang* conduits	Stabilising and regulating the *qi* of centre; strengthening the hepatic and pulmonal orb, keeping the nasal passages open	Cough and asthma
*Feishu* (UB 13)	1.5 *cun* laterally of the processus spinosus of the 3rd thoracic vertebrae	Dorsal inductor (inductorium dorsale) for the pulmonal orb	Stabilising and harmonizing the pulmonal and the renal orb; regulating the *qi*; strengthening the *yin*	Cough with asthma, common cold, nasal congestion
*Shenshu* (UB 23)	1.5 *cun* laterally of the 2nd lumbar vertebrae	Dorsal inductor of the renal orb	Strengthening and harmonizing the renal orb; improving hearing and clearing vision	Cough, asthma, asthenic breathing

### Outcomes

The primary outcome will be the change in the weekly average of the Total Nasal Symptom Score (TNSS) recorded in participants’ diaries from baseline to the end of treatment [22]. The TNSS consists of four nasal symptoms (rhinorrhea, nasal itching, nasal obstruction, and sneezing) using a five-point scale from 0 to 4 (0 = no symptom, 1 = mild, 2 = moderate, 3 = severe, 4 = very severe). The TNSS will be obtained from the sum of all four individual symptom scores, with a total possible score ranging from 0 (no symptoms) to 16 (maximum symptom intensity). This scoring system has been validated [23, 24].

The secondary outcomes will be changes in symptoms and changes in need for medication between baseline and the end of treatment. Symptoms will be assessed by using the RQLQ, which has 28 questions in seven domains (activity limitation, sleep problems, nasal symptoms, ocular symptoms, other symptoms, practical problems, and emotional function) ranked from 0 (no impairment) to 6 (severe impairment) [25]. Rescue medication need will be measured using an RM score (RMS), comprising the weekly sum of daily assessments. Rescue medicine usage will be scored daily on a four-point scale (0 = no rhinitis medicine; 1 = cetirizine, 10 mg/d, or equivalent; 2 = cetirizine, 20 mg/d, or equivalent; 3 = systemic or topical corticosteroids for AR) (daily range; 0 to 3; weekly range: 0 to 21). If more than one RM is used on the same day, only the maximal score medication will be recorded [26].

For safety concern, we will record every adverse event during the treatment and follow-up, and make statistical comparisons. Treatment will be suspended immediately should serious adverse events occur. Further assessment will be needed to decide whether the trial should be suspended.

### Randomization assignment

This study is designed as a randomized, waitlist-control trial. Eligible participants will be randomly and equally allocated to one of the three groups: T (TJ) group, P (placebo) group, and W (waitlist-control) group. Random Allocation Software (version 1.0.0, Isfahan, Iran) will be used to generate a randomization scheme. The principal investigator (PI) will generate the random allocation sequence, and will not share it with other investigators. After the run-in stage, a research assistant (RA) will assign treatments according to the codes which are kept in opaque sealed envelopes with consecutive randomization numbers. Emergency unblinding can only happen when the intervention information is compulsory for the participant’s future management.

### Sample size

Sample size calculations are based on the primary outcome measurement. Since this is a pilot clinical study, the improvement rate of group W would obviously be 0. Subsequently, we assume that there will be 30 % improvement of TNSS symptoms in group T and 15 % in group P. Considering a power of 80 %, and a alpha value of 2.5 % (two-tailed), the sample size will be calculated using the following formula:$$ n=\frac{2\lambda }{{\left(2{ \sin}^{-1}\sqrt{P_t}-2{ \sin}^{-1}\sqrt{P_w}\right)}^2}, $$

The λ is the cut-off value. *Pt* is 30 % and *Pw* is 0. Then each group will need at least 38 subjects for significance to be detected [27]. Allowing for a 20 % dropout, we plan to recruit 46 subjects in each group, making a total of 138.

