### Data processing and analysis

All efficacy and safety analyses will be conducted according to the intention-to-treat (ITT) principle. Missing values will be imputed by the last-observation-carried-forward method. The statistical analysis will be performed using the Statistical Packages for the Social Sciences (SPSS) for Windows, version 21.0. Statistical significance is defined as a two-sided *P* value of <0.05. Baseline characteristics will be reported as mean (SD). Comparisons between groups will be conducted by using an analysis of covariance (ANCOVA) with baseline as covariate. All items and subscales will be compared between groups for each 4-week period using ANCOVA, with treatment group as a factor in the model and baseline as the covariate. The changes in scores from baseline to the end-point of treatment will be tested using repeated measure analysis of variance (ANOVA). Within-group differences will be assessed using a paired *t* test for normally distributed data and a Wilcoxon signed-rank test for non-normally distributed data.

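### The sample size uses a formula for proportions, but the primary outcome is a score analysed as a score, so the stated 80 % power does not describe the planned analysis

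*Protocol article*

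**What the plan says.** Under Sample size, the protocol article opens with "Sample size calculations are based on the primary outcome measurement". It then states that "the improvement rate of group W would obviously be 0" and that "we assume that there will be 30 % improvement of TNSS symptoms in group T and 15 % in group P". With 80 % power and a two-tailed alpha of 2.5 %, it prints an arcsine square-root formula, enters 30 % for group T and 0 for group W, and reports at least 38 subjects per group. This becomes 46 per group, 138 in total, after an allowance for dropout.

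The Outcomes section defines the endpoint as follows: "The primary outcome will be the change in the weekly average of the Total Nasal Symptom Score (TNSS) recorded in participants’ diaries from baseline". The later time point is when treatment ends. The score is the sum of four symptom items and runs from 0 to 16.

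Under Data processing and analysis: "Comparisons between groups will be conducted by using an analysis of covariance (ANCOVA) with baseline as covariate". The same section adds: "The changes in scores from baseline to the end-point of treatment will be tested using repeated measure analysis of variance (ANOVA"). Significance there is two-sided at 0.05, and the analysis is by intention to treat with last observation carried forward (LOCF).

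**The concern.** The difference of two arcsine square roots is the effect size for comparing two binomial proportions. It needs the probability that a patient counts as improved. The primary outcome instead yields a mean and an SD for each group. A calculation for that outcome needs a difference in TNSS points and an SD, and the article gives neither.

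The phrase about 30 % improvement can be read in two ways, and the mismatch survives both:

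- If 30 % of patients are expected to improve, the trial is sized for a binary endpoint that none of its listed analyses uses.
- If the mean score is expected to fall by 30 %, a percentage change in a mean has been entered where the formula requires a probability.

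The opening sentence of the Sample size section is therefore incorrect as written, and the only power statement in the article does not apply to the analysis it introduces. In practice, nobody can say from this plan what TNSS difference the trial can detect, or how informative a null result would be.

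**Working it through.** **1. The plan's own figure.** The printed formula is n = 2λ / (2 asin√Pt − 2 asin√Pw)².

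- Pt = 0.30 and Pw = 0 give an effect size of 2 asin√0.30 = 1.159, whose square is 1.344.
- For two groups at 80 % power and two-sided alpha 0.025, λ = (2.241 + 0.842)² = 9.51. Then n = 2 × 9.51 / 1.344 = 14.1, so 15 per group.
- With λ for a three-group test (df = 2), λ = 11.49 and n = 17.1, so 18 per group.
- A result of 38 would need λ = 38 × 1.344 / 2 = 25.5.

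The printed inputs do not return 38 under these readings of λ. That is a separate defect. Here it shows only that 38 cannot be defended as a proportions calculation either.

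**2. What 38 or 46 per group can detect on a score.** Two-sample t test, equal groups, 80 % power, no baseline adjustment. The approximate formula is d = (z for alpha + z for power) × √(2/n). For n = 38 it gives (1.960 + 0.842) × √(2/38) = 0.643 at 0.05 and (2.241 + 0.842) × √(2/38) = 0.707 at 0.025. The exact noncentral t values are slightly larger:

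| Analysed per group | two-sided 0.05 | two-sided 0.025 |
|---|---|---|
| 38 | 0.65 SD | 0.72 SD |
| 46 | 0.59 SD | 0.65 SD |

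**3. Illustration in TNSS points.** The article gives no baseline mean and no SD, so both are assumptions: a baseline mean of 10 (Inclusion criteria set a floor of 8) and an SD of change of 2, 3 or 4 in every group. Read 30 %, 15 % and 0 as mean reductions. T versus W is then 0.30 × 10 = 3.0 points, and T versus P is (0.30 − 0.15) × 10 = 1.5 points. Power with 38 per group (exact t), for SD 2 / 3 / 4:

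| Contrast | d | at 0.05 | at 0.025 |
|---|---|---|---|
| T vs W | 1.50 / 1.00 / 0.75 | >99 / 99 / 90 % | >99 / 98 / 83 % |
| T vs P | 0.75 / 0.50 / 0.375 | 90 / 58 / 36 % | 83 / 46 / 26 % |

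**4. Sensitivity to the assumed baseline** (normal approximation, 38 per group). At a mean of 8, the entry floor, T versus W is 2.4 points, and with SD 4 its power is 74 % at 0.05 and 65 % at 0.025. At a mean of 12, T versus P is 1.8 points, and its power at 0.05 is 98 / 74 / 50 % for SD 2 / 3 / 4.

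**5. Baseline adjustment.** Let r be the correlation between baseline and follow-up scores, with equal variances σ². ANCOVA has residual variance σ²(1 − r²). The change score has variance 2σ²(1 − r). The ratio of the two is (1 + r)/2. Against an SD of change, the variance factor is therefore 0.65 at r = 0.3, 0.75 at r = 0.5 and 0.85 at r = 0.7. Using 1 − r² there instead would give 0.91, 0.75 and 0.51, which is wrong except at r = 0.5. With r = 0.5 assumed, T versus P power at 0.05 in step 3 rises to 96 / 70 / 46 %.

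**The case against.** The strongest reply is that the low power figures belong to another issue. The Sample size section enters only T versus W, and in every scenario of step 3 that contrast exceeds 80 %. The shortfalls concern T versus P, which was never sized and would fall short even with the proportions formula used consistently: 30 % versus 15 % with 38 per group gives about 35 % power at 0.05 and 26 % at 0.025. This stands. A reader might infer from the mismatch that the trial is underpowered. The article does not support that, because the answer turns on a baseline mean and an SD that it does not give.

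Three further replies have partial force.

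- Intention to treat with LOCF would analyse up to 46 per group rather than 38. T versus P power at 0.05 then becomes about 94 / 66 / 43 %. This is a best case, because it counts carried-forward values as full information.
- A reader might take ANCOVA to be the designated primary test. The article names no single primary test, and its sentence on change from baseline to end-point assigns repeated-measures ANOVA. The mismatch does not depend on the choice, since both methods analyse scores.
- This is a condensed article that speaks of an improvement rate and never of responders, so the absence of a responder definition is weak evidence. It is not needed: the formula, its inputs and the outcome are all printed.

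The article also calls the study a pilot and, under Background, a basis for a larger trial. That softens the consequence, but the same article claims 80 % power and expects consolidated evidence of effectiveness.

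**Conclusion.** The point holds as a mismatch between the sample-size method and the outcome it claims to serve. It rests only on printed text and needs no assumption about baseline or SD: a proportions formula cannot give the power of an analysis of mean TNSS change, so the stated 80 % has no basis for the planned analysis.

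The finding stops short of saying that power is too low. Under the assumed baseline of 10 and SD of change of 2 to 4, power with 38 per group and no baseline adjustment is at least 83 % at 0.025 for the contrast that was sized. It lies anywhere between 90 % and 36 % at 0.05 for the placebo contrast that was not. Other baseline values shift both ranges, as step 4 shows.

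**What to change.** Replace the proportions formula with a calculation for the mean TNSS change at the end of treatment. Name the contrast being sized, the difference in TNSS points, and an SD with its source.

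If no SD can be found, withdraw the 80 % claim and state what the fixed size delivers before baseline adjustment. With 38 completers per group, that is 80 % power for a standardised difference of about 0.65 (two-sided 0.05) or 0.72 (0.025). If all 46 are analysed, it is at best 0.59 or 0.65.

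If a gain from ANCOVA is claimed, apply 1 − r² to the variance of the end-of-treatment score, with r the baseline to follow-up correlation. Do not apply it to the SD of change.

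The cost is one rewritten paragraph. The total of 138 can stay, provided the text says plainly what it can detect. Trial status reports that no patient had begun treatment at submission, so the correction can precede any data.

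### The stated 38 per group does not follow from the printed formula and inputs (which give 15 or 18), and 46 per group does not keep 38 after 20 % dropout

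*Protocol article*

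**What the plan says.** All of this is in the Sample size section of the protocol article. The waitlist rate is fixed first: "Since this is a pilot clinical study, the improvement rate of group W would obviously be 0". Rates for the other two arms follow: "we assume that there will be 30 % improvement of TNSS symptoms in group T and 15 % in group P". Power is 80 % and alpha is 2.5 %, two-tailed. The printed formula is n = 2 lambda / (2 arcsin √Pt − 2 arcsin √Pw)², with Pt = 30 % and Pw = 0. Lambda is described only as a cut-off value and has no number. The result is: "Then each group will need at least 38 subjects for significance to be detected". The dropout step is: "Allowing for a 20 % dropout, we plan to recruit 46 subjects in each group, making a total of 138".

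**The concern.** The article prints the formula, both rates, alpha, power and the answer, so a reader can check the sum. Only lambda has to be supplied, and alpha and power determine it once the number of groups compared is settled. The sum does not come out at 38 on either reading. This paragraph is the only justification for enrolling 138 people, and as printed its figure cannot be traced.

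Two further weaknesses affect the same figure. The calculation rests on a waitlist rate of exactly zero, and pilot status, the only reason given, has no bearing on how untreated patients fare. The arcsine difference also changes fastest near zero, so a small change in that rate moves n a great deal. Finally, the dropout allowance multiplies by 1.2 where it should divide by 0.8, so it falls short of the minimum that the plan itself sets.

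**Working it through.** **Inputs.** From Sample size: Pt = 0.30, Pw = 0, power 0.80, two-tailed alpha 0.025, stated n = 38, dropout 20 %, 46 per group, 138 in total. From Randomization assignment: equal allocation to three groups. Lambda is not given, so I take it as the noncentrality that yields 80 % power at alpha 0.025. The rates are read as proportions, as the formula requires.

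**Lambda.**
- Two groups (1 df): (2.2414 + 0.8416)² = 9.505
- Three groups (2 df, noncentral chi-square): 11.493

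**Attempt to reproduce 38.** 2 arcsin √0.30 = 1.1593, the Pw term is 0, and 1.1593² = 1.3439.
- Two-group: 2 × 9.505 / 1.3439 = 14.15, so 15 per group
- Three-group: 2 × 11.493 / 1.3439 = 17.10, so 18 per group
- With the two-sided 5 % level from Data processing and analysis, lambda is 7.85 or 9.63, and n is 12 or 15

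Other standard methods for 30 % against 0 at two-sided 2.5 % and 80 % power also miss 38: pooled normal 26, continuity-corrected 32, Fisher exact 25.

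**What 38 would imply.** Lambda = 38 × 1.3439 / 2 = 25.5. In the two-group case √25.53 − 2.2414 = 2.81, which is power of 99.8 %. In the three-group case it is 99.3 %. The plan states 80 %.

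**Sensitivity to the waitlist rate.** The rates below are an assumed range, because the protocol gives no waitlist data. Two-group lambda, alpha 0.025:

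| Pw | squared arcsine difference | n per group at 80 % power | power at 38 per group |
|---|---|---|---|
| 0 | 1.3439 | 14.15 → 15 | 99.8 % |
| 1 % | 0.9196 | 20.7 → 21 | 97 % |
| 5 % | 0.5016 | 37.9 → 38 | 80 % |
| 10 % | 0.2660 | 71.5 → 72 | 50 % |

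With the three-group lambda, Pw = 5 % needs 2 × 11.493 / 0.5016 = 45.8 per group, and power at 38 is about 71 %.

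**Dropout.**
- 38 × 1.2 = 45.6, which rounds up to the planned 46
- 46 × 0.8 = 36.8, below 38
- 38 / 0.8 = 47.5, so 48 per group and 144 in total
- Loss that 46 can absorb while keeping 38: 1 − 38/46 = 17.4 %

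**The case against.** The strongest reply is that nothing is lost. On the printed inputs 38 is more than enough: power at 36 to 38 per group is about 99 % or more with either lambda. This stands. A reader might infer that TJ versus waitlist is underpowered, but the documents do not support that. Power falls below 80 % only if the waitlist rate is some way above zero, and the protocol supplies no such rate. Features of the design make zero far from obvious: entry requires a TNSS of 8 or more, intermittent disease is eligible, and rescue medication is allowed in every arm. They do not give a number.

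A reader might also infer that the authors used a waitlist rate of 5 %, because it gives 37.9. That is back-solved. It fails with the three-group lambda (45.8), and other unstated inputs come as close. With the 5 % rate, three groups and alpha 0.05, n is 38.4; pooled 15 % against 0 at one-sided 0.05 gives 38. The coincidence shows why disclosure is needed, not what was done.

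On dropout, it can be said that the analysis is by intention to treat with last observation carried forward, so those who leave may still be analysed, and that the gap is about one patient per arm. The gap is indeed small. But the plan chose to make an allowance, set 38 as the minimum, and then computed the allowance wrongly; the imputation rule does not correct that sum.

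It is also fair to say that repairing this paragraph leaves other questions open. The formula compares proportions while the primary outcome is a continuous change in TNSS, the TJ versus placebo contrast is not sized, and alpha is 2.5 % here but 5 % in the analysis section. Those are separate points.

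**Conclusion.** The point holds as a defect of traceability. The printed formula and inputs give 15 or 18 per group against a stated 38, more than double, and rounding cannot explain it. Either an undisclosed input was used or the result is wrong; the article does not let a reader tell which. This rests on lambda having its usual meaning, and both usual values lead to the same conclusion.

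The zero waitlist rate is unsupported by the reason given. Whether it is false cannot be settled from the documents. What can be shown is its leverage: over an assumed 0 to 10 %, the two-group requirement runs from 15 to 72 per group, and power at 38 runs from 99.8 % to 50 %.

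The dropout slip is certain but small: 36.8 remaining against a stated minimum of 38, or 46 per group where 48 would be needed (138 against 144 in total).

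**What to change.** Rewrite the Sample size paragraph as follows.

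1. State the numerical lambda and whether it is the two-group or three-group value, state the waitlist rate actually entered, and make the stated n agree with them. The authors should supply that rate from their own records; a reviewer's back-solved 5 % should not be written in for them.
2. Replace the statement that "the improvement rate of group W would obviously be 0" with an explicit assumption, and give the power at the planned n for a range of waitlist rates such as 0, 5 and 10 %.
3. Keep 138, but either describe the allowance as about 17 % dropout or say that 36 to 37 completers per arm remain at 20 % and give the power at that number. On the two-group lambda this is above 99 % at a waitlist rate of 0 and about 78 to 79 % at an assumed 5 %.

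The cost is the rewording of one paragraph and possibly a less favourable stated power. No extra patients are needed, and according to Trial status no patient had begun treatment when the article was submitted.

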### Data processing and analysis

All efficacy and safety analyses will be conducted according to the intention-to-treat (ITT) principle. Missing values will be imputed by the last-observation-carried-forward method. The statistical analysis will be performed using the Statistical Packages for the Social Sciences (SPSS) for Windows, version 21.0. Statistical significance is defined as a two-sided *P* value of <0.05. Baseline characteristics will be reported as mean (SD). Comparisons between groups will be conducted by using an analysis of covariance (ANCOVA) with baseline as covariate. All items and subscales will be compared between groups for each 4-week period using ANCOVA, with treatment group as a factor in the model and baseline as the covariate. The changes in scores from baseline to the end-point of treatment will be tested using repeated measure analysis of variance (ANOVA). Within-group differences will be assessed using a paired *t* test for normally distributed data and a Wilcoxon signed-rank test for non-normally distributed data.

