## Methods/design

### Study design

This will be a prospective, randomized, single-blinded, controlled trial in patients with AR. After a 1-week run-in period, eligible subjects will be randomly assigned to the TJ group, placebo-control group or waitlist-control group. Except for rescue medication (RM) drugs, no other routine medication use for AR symptom control will be permitted in the entire study.

The TJ group will undergo a 4-week treatment with herbal patches for one session per week, and a 4-week post-treatment follow-up of one assessment session per week. The placebo-control group will undergo a 4-week treatment with placebo patches for one session per week, and a 4-week post-treatment follow-up of one assessment session per week. The waitlist-control group will receive no treatment during the first 4 weeks but, beginning at the fifth week, this group will receive TJ treatment for 4 weeks as compensatory. All groups will be assessed in the same way throughout the study period. The total study period will be 9 weeks. The participant flowchart is listed in Fig. 1 and participant timeline is listed in Fig. 2.

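### Safety is placed under intention-to-treat alone, and the LOCF rule that follows is not confined to efficacy scores, so absolute harm rates could be modestly diluted

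*Protocol article*

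**What the plan says.** Three statements in the protocol article bear on this.

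- Data processing and analysis sets one principle for benefit and harm: "All efficacy and safety analyses will be conducted according to the intention-to-treat (ITT) principle".
- The sentence directly after it reads: "Missing values will be imputed by the last-observation-carried-forward method". It names no variable type and is not restricted to symptom, quality-of-life or rescue-medication scores.
- Outcomes makes harms a formal comparison: "we will record every adverse event during the treatment and follow-up, and make statistical comparisons".

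The Abstract names safety as an aim alongside efficacy. Sample size expects attrition: "Allowing for a 20 % dropout, we plan to recruit 46 subjects in each group".

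No section defines a set of participants by exposure or gives a separate missing-data rule for adverse events. None gives an expected adverse-event rate or the number likely to be randomised but never patched.

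**The concern.** For efficacy, analysing everyone as randomised protects the comparison. For harms, a participant who never wore a patch cannot have a patch reaction, yet still counts in the denominator. The reported absolute rate falls, and with similar non-exposure in both arms so does the TJ-placebo difference. Any participant given the other arm's patch would be counted under the assigned arm.

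LOCF suits scheduled scores. Applied to an adverse-event status, it turns unobserved weeks into observed ones: a dropout who was clear at the last visit becomes event-free for the remaining weeks, and one who left with a reaction has it repeated. Because the LOCF sentence comes straight after one that names safety analyses, an analyst could apply it that way.

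At stake is how accurately the trial reports TJ's absolute harm rate, which is part of its stated aim. The primary efficacy result is not affected.

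**Working it through.** **Plan's own figure.** The article states no safety figure, so there is none to reproduce. What follows sizes the effect under assumptions.

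**Inputs**

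| Input | Value | Source |
|---|---|---|
| Participants per arm | 46 | Sample size |
| Dropout | 20 %, i.e. 0.20 × 46 = 9.2, about 9 per arm | Sample size |
| Significance level | 0.05 two-sided | Data processing and analysis |
| Sessions | 4, one per week | Study design |
| Never-exposed share *u* | 0 to 20 % | Assumed; not in the article |
| True event rates | TJ 30 %, placebo 5 % | Assumed; not in the article |
| Event chance per session (LOCF step) | 10 % | Assumed; not in the article |

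**Step 1: dilution from the denominator.** If a share *u* of an arm is never patched and so has no patch-related events, the by-allocation rate is true rate × (1 − *u*). With *u* equal in both arms:

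| *u* | TJ | Placebo | Difference (points) | Ratio |
|---|---|---|---|---|
| 0 | 30 % | 5 % | 25 | 6 |
| 2 % | 29.4 % | 4.9 % | 24.5 | 6 |
| 5 % | 28.5 % | 4.75 % | 23.75 | 6 |
| 10 % | 27 % | 4.5 % | 22.5 | 6 |
| 20 % | 24 % | 4 % | 20 | 6 |

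The factor (1 − *u*) cancels in the ratio. If the shares differ, the difference is 0.30(1 − *u*_T) − 0.05(1 − *u*_P). With *u*_T = 20 % and *u*_P = 0 it is 24 − 5 = 19 points. With the shares reversed it is 30 − 4 = 26 points. Shrinkage of the difference is therefore the usual result but not a certain one.

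**Step 2: effect on the test.** On the same assumed rates at *u* = 20 %, power is 80.0 % by allocation (24 % vs 4 %, 46 per arm). It is 81.9 % in exposed participants only (30 % vs 5 %, 0.8 × 46 = 36.8 per arm). The comparison loses little power; what changes is the reported rate.

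**Step 3: LOCF, only if applied to adverse events.** Suppose 20 % leave after session 1 and the other 80 % have a 10 % event chance in each of four weeks, so 0.8 × 4 × 0.10 = 0.32 event-weeks per randomised person. Sessions delivered per person are 0.8 × 4 + 0.2 × 1 = 3.4.

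- *All leavers had an event in week 1.* Recorded: 0.32 + 0.2 × 1 = 0.52 event-weeks, or 0.52 / 3.4 = 15.3 % per session delivered. Carried forward: 0.32 + 0.2 × 4 = 1.12 event-weeks, or 1.12 / 4 = 28 % per planned week.
- *No leaver had an event.* Recorded: 0.32, or 0.32 / 3.4 = 9.4 % per session delivered. Carried forward: 0.32 spread over four planned weeks, or 8 %.

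LOCF raises the weekly rate in the first case and lowers it in the second, so its direction depends on why people leave.

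**The case against.** **LOCF on events is a reading, not a statement.** The analyses described after the LOCF sentence are all of scores: ANCOVA with baseline as covariate, items and subscales, repeated-measures ANOVA and paired tests. An adverse-event log has no baseline value to carry. A reader might infer that the plan will impute adverse events, but no section says so. What stands is an ambiguity created by the placement and breadth of the sentence.

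**Non-exposure may be rare.** Allocation follows the run-in, so losses during run-in never enter the randomised set, and anyone who leaves after a first session has been exposed. Nothing suggests that wrong patches are expected. The 20 % figure is an extreme bound.

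**ITT does not explain the whole shortfall from full-course risk.** A reader might charge ITT with the entire gap between the risk after four sessions and the rate reported with dropouts. At 10 % per session, four-session risk is 1 − 0.9⁴ = 34.4 %. With 20 % dropout split evenly over 0, 1, 2 or 3 sessions, the by-allocation rate is 0.8 × 0.3439 + 0.2 × (0 + 0.100 + 0.190 + 0.271)/4 = 30.3 %. Restricting to those with at least one session gives 0.3032 / 0.95 = 31.9 %. The denominator thus explains about 1.6 of the 4.1 points; the remaining 2.5 come from early stopping, which an at-least-one-session set keeps. A per-session result is needed for that part.

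**ITT for harms is legitimate.** It is a valid randomised contrast, and detail on safety sets is often left to a statistical analysis plan. The first half is right, which is why the by-allocation analysis can be kept. The second half does not settle the matter: the article states a rule that covers all safety analyses, and a later plan would have to contradict it.

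**Conclusion.** The point holds as a minor one. The article fixes ITT as the only principle for safety and follows it with an LOCF rule that is not limited to scores.

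The consequence of the first is a dilution of absolute harm rates by the never-exposed share: 2-5 % in relative terms if few are never patched, and no more than 20 % if every planned dropout leaves before the first session. The risk ratio is unchanged when the share is equal in both arms. The consequence of the second is conditional on LOCF being applied to adverse events, and its sign cannot be predicted. All event rates and exposure shares used here are assumptions.

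The article does not support a claim that TJ's harms will be seriously understated.

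A separate matter lies outside this TJ-placebo point. For the waitlist arm, "beginning at the fifth week, this group will receive TJ treatment for 4 weeks as compensatory", so a by-allocation safety comparison over the whole study would count TJ events under waitlist.

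**What to change.** In Data processing and analysis:

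1. Confine the ITT sentence to efficacy analyses and the LOCF sentence to efficacy scores.
2. State that adverse events are analysed as observed, without imputation, in participants who received at least one patch session, grouped by the patch actually received.
3. Report two results: participants with at least one event, and events per session delivered. The second accounts for early stopping, which the first does not.
4. If wanted, keep a by-allocation comparison of TJ and placebo beside these.
5. Tabulate events during the waitlist arm's deferred TJ course separately, so that grouping by patch received does not merge them into the randomised TJ-placebo comparison.

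The cost is a few sentences, provided the sessions each participant receives are logged. The reported TJ adverse-event rate may be slightly less favourable. Trial status says no patient has begun treatment, so the change can be made before any data exist.
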